### Secondary objectives

To determine the effectiveness of bathing adaptations compared to no adaptations on the secondary outcomes of mental well-being, self-reported falls, health and social care services and resource use, health-related quality of life, social care-related quality of life, perceived risk of falling, independence in daily activities, independence in bathing and perceived difficulty in bathing.To carry out an extended follow-up of participants over a 12-month period in order to determine the effect of waiting times on outcomes and resource use.To conduct an economic evaluation to determine the cost-effectiveness of bathing adaptations compared to no bathing adaptations and expedited versus routine provision of bathing adaptations.To carry out a mixed-method process evaluation involving a range of stakeholders in order to explore and evaluate trial systems and process and the factors associated with the implementation of expedited and routine provision of bathing adaptations.

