#### Intervention description {11a}

##### Control

Bathing adaptation within the usual timescale. The participant will undergo the usual process and timescales for receiving a bathing adaptation and be allocated to a project officer/surveyor to begin the adaptation process when they reach the top of the waiting list and/or by the usual processes and timescales within the local authority.

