### Outcomes {12}

The use of pairwise randomisation means that the timing of the follow-up for each pair can be based on the completion of the bathing adaptations. For each randomised pair, participant follow-up data will be collected at three points: (1) 4 weeks after the intervention participant receives their bathing adaptation, (2) 4 weeks after the control participant receives their bathing adaptation or at 9 months (whichever is sooner) and (3) 12 weeks after the control participant receives their bathing adaptation, or at 12 months (whichever is sooner). For some participants recruited early in the study, data were collected 2 weeks before the planned installation date of the bathing adaptation in the control group participant, where possible; however, a protocol amendment was approved to remove this follow-up as the majority of participants were not completing this due to the dates of their showers being installed or difficulty getting the dates in time to schedule the follow-up. We will follow the majority of participants for 12 months; however, for the participants recruited at the end of the trial, we will follow them for 9 months (i.e., follow-up will continue for 9 months from the randomisation of the final participants).

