#### Secondary outcomes

All secondary outcomes are collected at baseline and each of the follow-up time points:Perceived mental health status measured via the Mental Component Summary score (MCS) of the SF-36 [19, 20].Number of falls (self-reported).Health and social care service use and associated costs (will be captured using a purposely designed and tested resource use questionnaire).Health-related quality of life using the EuroQol EQ-5D-5L [21].Social care-related quality of life using the Adult Social Care Outcomes Toolkit (ASCOT) [16].Perceived risk of falling (Short Falls Efficacy Scale) [22].Independence in bathing (bathing question of the Barthel Index) [23].Ability to manage personal activities of daily living (Barthel Index) [23]. This analysis will include those who could not complete the SF-36 at baseline.Perceived difficulty in bathing (0–100 scale).Incremental cost per quality-adjusted life year (QALY) gained.

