Other continuous secondary outcomes (e.g. SF-36 MCS, ASCOT, Barthel Index and FES-I) will be analysed using the same methods as the primary analysis; however, these analyses will also include those who could not complete the SF-36 at baseline. The number of falls experienced over the follow-up period will be compared between the groups using negative binomial regression adjusting for site and property tenure, and accounting for length of follow-up.

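### The only falls analysis counts the whole follow-up, so it compares expedited with routine provision and understates the adaptation-versus-none effect that the objective names

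*Protocol article*

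**What the plan says.** Under Secondary objectives, falls belong to the first aim: "To determine the effectiveness of bathing adaptations compared to no adaptations on the secondary outcomes of mental well-being, self-reported falls". A separate aim concerns delay: "To carry out an extended follow-up of participants over a 12-month period in order to determine the effect of waiting times on outcomes".

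Under Statistical analysis, one falls comparison is given: "The number of falls experienced over the follow-up period will be compared between the groups using negative binomial regression". Its only named covariates are site and tenure, and exposure enters solely through the phrase "accounting for length of follow-up". Nothing there distinguishes time with a shower from time without one, and neither baseline falls nor capacity is among the stated covariates.

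Controls are also adapted. The Control section says "The participant will undergo the usual process and timescales for receiving a bathing adaptation", and under Outcomes {12} the last assessment falls "12 weeks after the control participant receives their bathing adaptation, or at 12 months (whichever is sooner").

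Falls data exist at the points needed for a narrower comparison: "All secondary outcomes are collected at baseline and each of the follow-up time points".

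**The concern.** For the primary outcome, the protocol ties adaptation versus no adaptation to the first follow-up, when the intervention participant has a shower and the control participant normally does not. The mixed model delivers that contrast through a treatment-by-time interaction, with the baseline score as covariate. The other continuous secondary outcomes inherit the model. Falls inherit neither feature: there is one total per participant, with no period term and no baseline count.

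The total mixes three kinds of time: both arms unadapted, intervention only adapted, and both adapted. Only the middle period bears directly on the stated objective. A real reduction in falls could therefore be reported as small or absent, on an outcome that the Background uses to motivate the trial.

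**Working it through.** **Inputs from the article.** Follow-up 1 is 4 weeks after the intervention shower. Follow-up 2 is 4 weeks after the control shower or at 9 months, whichever is sooner. Follow-up 3 is 12 weeks after the control shower or at 12 months, whichever is sooner. No figure for falls is stated, so there is none to reproduce.

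**Assumptions, for illustration only.** The fall rate is constant and is multiplied by θ once a shower is in place. θ = 0.74 borrows the 26% reduction in Background and rationale, which concerned injuries from falls after minor adaptations, not fall counts after showers. The shower times T_I (intervention) and T_C (control) are assumed. One month = 52/12 weeks.

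**Formula.** For a window of length L in which the arms spend A_I and A_C weeks adapted:

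expected ratio = [(L − A_I) + θ·A_I] / [(L − A_C) + θ·A_C]

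**Whole follow-up, ending at the smaller of T_C + 12 weeks and 52 weeks.**

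- 3/8 months: L = 46.67, A_I = 33.67, A_C = 12. (13.00 + 0.74 × 33.67)/(34.67 + 0.74 × 12) = 37.91/43.55 = 0.87.
- 2/6 months: L = 38.00, A_I = 29.33, A_C = 12. 30.37/34.88 = 0.87.
- 2/4 months: L = 29.33, A_I = 20.67, A_C = 12. 23.96/26.21 = 0.91.

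Outcomes {12} also says that most participants are followed for 12 months. If everyone had a flat 12 months, the same three cases would give 0.88, 0.90 and 0.95.

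**Three candidate windows compared.** All use θ = 0.74.

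| Showers (intervention/control) | Whole follow-up | Randomisation to follow-up 1 | Follow-up 1 to follow-up 2 |
|---|---|---|---|
| 3/8 months | 0.87 | 0.94 | 0.78 |
| 2/6 months | 0.87 | 0.92 | 0.79 |
| 2/4 months | 0.91 | 0.92 | 0.84 |
| 8/20 weeks | 0.89 | 0.91 | 0.81 |
| 12/26 weeks | 0.90 | 0.94 | 0.80 |
| 12/39 weeks | 0.85 | 0.94 | 0.74 |
| 20/52 weeks | 0.84 | 0.96 | 0.74 |

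Example for the middle column, 3/8 months: L = 17 weeks, of which only 4 are adapted in the intervention arm; (13 + 0.74 × 4)/17 = 0.94.

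Example for the last column, 8/20 weeks: the window is weeks 12 to 24. The intervention arm is adapted throughout, 0.74 × 12 = 8.88. Controls have 8 unadapted and 4 adapted weeks, 8 + 2.96 = 10.96. The ratio is 0.81. The 2/4-month case is the weakest because the window is short (8.67 weeks, of which 4 are adapted in controls): 6.41/7.63 = 0.84.

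**Where the dilution comes from.** With showers at weeks 12 and 39, the intervention arm's wait alone moves 0.74 to 0.80 (41.6/52, control not fitted within 12 months). The control showers move it on to 0.85. Both parts matter, and a control who is never fitted during follow-up adds none of the second part.

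**The case against.** The strongest defence is that the whole-period count has a legitimate use. The waiting-time aim asks how delay affects outcomes over 12 months, and an intention-to-treat count with exposure accounted for answers that. This stands. The analysis is valid for that aim; the fault is that it is the only falls analysis and that falls are named under the other aim.

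It can also be said that the article defers to a detailed analysis plan. That carries weight for the covariates: baseline falls and capacity may yet be added there. It carries less for the window, because the article itself fixes the period, the model and the exposure adjustment.

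Three stronger readings are tempting and not supported:

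- A reader might infer that leaving out baseline falls helps to dilute the effect. Under randomisation, omitting a baseline covariate costs precision and protection against chance imbalance. It neither mixes adapted with unadapted time nor changes the objective answered.
- A reader might infer that falls are the only secondary outcome without a follow-up 1 contrast. The article extends the primary model to other continuous secondary outcomes only, and its examples do not include the single bathing item or service use.
- A reader might infer that cutting the count at follow-up 1, as for the primary endpoint, would cure the problem. It would not: that window holds about 4 adapted intervention weeks, and in every case in the table its ratio lies nearer 1 than that of the planned analysis.

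**Conclusion.** The mismatch is real: the falls objective is adaptation versus none, and the stated analysis estimates expedited versus routine provision. Under the follow-up 3 end rule and a true ratio of 0.74, the expected whole-period ratio is 0.84 to 0.91 across the assumed waits in the table. The direction of the bias does not depend on the exact waits, provided that the intervention arm waits at all or some controls are fitted during follow-up. The size does, and the article gives no waits, fall rate or dispersion, so these figures illustrate the problem and do not forecast the trial's result.

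The omission of baseline falls and capacity is a separate and smaller matter of precision. Capacity is a randomisation stratifier, and participants lacking capacity contribute falls data through an alternative participant, so both variables are already to hand. This should be changed, but it does not threaten the primary result.

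**What to change.** 1. Keep the whole-follow-up negative binomial count and label it as the expedited-versus-routine analysis under the waiting-time objective.
2. For adaptation versus no adaptation, add a negative binomial comparison by randomised group of falls reported between follow-up 1 and follow-up 2, with log person-time as offset. A by-period model with a group-by-period interaction would serve equally. For early recruits who had the extra visit between these two points, add its count to the interval.
3. Adjust both analyses for baseline falls and capacity stratum, besides site and tenure.
4. Do not make randomisation to follow-up 1 the main falls window. Do not require a pair term: under Sequence generation {16a}, some participants who cannot complete the primary outcome may be randomised without a pair.

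The cost is analysis wording, settled before data collection ends. The added comparison has fewer falls and a wider interval. It assumes that each report covers the time since the previous one, which the article does not state. Some dilution remains because controls fitted before 9 months are adapted for up to 4 weeks before follow-up 2; this matters most where the two showers come close together, as in the 2/4-month case. Starting and stopping at the installation dates would be sharper, but the article describes fall counts and not fall dates.

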#### Health economic analysis

Both cost-effectiveness and cost-utility analyses will be conducted from personal health and social care services and a societal perspective including carers and paid care workers. The cost-utility analysis will be based on EQ5D-5L quality-adjusted life years (QALYs) and both will estimate costs. Secondary cost-effectiveness will be conducted using the Adult Social Care Outcomes Toolkit (ASCOT). Our analysis will take both personal health and social services and a societal perspective as we expect costs and savings will also accrue to family members. Incremental cost-effectiveness ratios (ICER) and cost-effectiveness acceptability curves (CEACs) will be produced using each outcome measure for the expedited adaptations versus usual waiting time control, at each time point and uncertainty will be explored.

Furthermore, aiming to strengthen the alignment between data analysis and decision-making processes, we will estimate the return on investment (ROI) for expedited adaptations versus usual waiting time control and build a ROI tool for use by decision-makers involved in commissioning and provision in home adaptation services. ROI is a form of economic evaluation that values the financial return, or benefits, of an intervention against the total costs of its delivery [28]. This ROI tool will extend the work conducted regarding the ROI for housing adaptations in relation to falls on stairs (reported in Powell et al. [12] and will estimate the ROI for improved waiting times and reduced delay. The benefit minus the cost expressed as a proportion of the cost will be estimated and the results will be used to parameterise a ROI toolkit using Microsoft® Excel [29]. This spreadsheet-based toolkit will estimate the costs and consequences of improving waiting times according to local characteristics and assumptions, such as prevalence and uptake of adaptations.

### Interim analyses {21b}

There are no planned interim analyses and no planned stopping rules for this trial.

### Methods for additional analyses (e.g. subgroup analyses) {20b}

A sensitivity analysis will be conducted, excluding any participants who indicated that they had COVID-19 within the course of the trial follow-up period to explore the potential effects that COVID-19 may have had on the outcomes.

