#### Primary outcome

The primary outcome is in physical health status, measured using the Physical Component Summary (PCS) score of the SF-36 [19, 20]. The SF-36 is a generic measure of perceived health status and quality of life, which can be used across a range of medical conditions and disabilities. Its selection is based on the inclusion of the physical functioning subscale and is informed by the findings from the BATH-OUT-1 feasibility study [10, 14] and consultation with our Public and Person Involvement (PPI) group. The primary analysis will compare the PCS score of the SF-36 between the two groups, excluding the group lacking the mental capacity to complete it. The primary endpoint is the first follow-up assessment, which is 4 weeks post-adaptation in the intervention group, to evaluate the effect of adaptation versus no adaptation. Data from later time points will be used to address the secondary objectives.

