**Fig. 2 Fig2:**
[figure not shown]
Schedule of enrolment, interventions and assessment. *Some participants enrolled early in the trial had an additional follow-up between t1 and t2 before the intervention was provided in the routine adaptation group. This follow-up has now been removed from the current version of the protocol

At baseline, participants who are able to answer questions themselves will complete a questionnaire comprised of participant demographics, property tenure, COVID-19 status and several outcome measures: the SF-36 [19, 20], number of falls, a health and social care service and resource use questionnaire, the EQ-5D-5L [21], the ASCOT questionnaire [16], the short Falls Efficacy Scale (FES) [22], the Barthel Index [23] and the bathing question of the Barthel Index [23]. If the participant lacks mental capacity, the alternative participant will complete a shortened questionnaire comprising participant demographics, property tenure, COVID-19 status and several outcome measures including number of falls, a health and social care questionnaire, the EQ-5D-5L (proxy version 2) [24], the Barthel Index [23], the bathing question of the Barthel Index [23] and perceived difficulty in bathing.

Similarly, at the three subsequent data collection time points, participants who are able to answer questions themselves will complete a questionnaire comprised of the SF-36 [19, 20], number of falls, a health and social care service and resource use questionnaire, the EQ-5D-5L [21], the ASCOT questionnaire [16], the short FES [22], the Barthel Index [23] and the bathing question of the Barthel Index [23]. If the participant lacks mental capacity, the alternative participant will again complete shortened questionnaire comprising a number of falls, a health and social care questionnaire, the EQ-5D-5L (proxy version) [24], the Barthel Index [23], the bathing question of the Barthel Index [23] and perceived difficulty in bathing.

Participants will be sent a ‘diary’ to complete following the first follow-up visit and after each subsequent follow-up visit to enable them to record contacts with health, social care and other services. This diary will be optional, for them to complete at home. The purpose is to aid their recall where there is a longer time period between each follow-up. The diary will not be returned to the research team.

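### The COVID-19 sensitivity analysis drops whole participants for infection at any time in follow-up, so it discards primary-endpoint scores measured before the infection

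*Protocol article*

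**What the plan says.** Methods for additional analyses {20b} describes a single sensitivity analysis, "excluding any participants who indicated that they had COVID-19 within the course of the trial follow-up period", to explore what COVID-19 may have done to the outcomes. The unit excluded is the participant. The article does not limit the rule to infection before a given assessment.

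On the endpoint, Outcomes {12} says: "The primary endpoint is the first follow-up assessment, which is 4 weeks post-adaptation in the intervention group". On duration, the same section says "We will follow the majority of participants for 12 months; however, for the participants recruited at the end of the trial" it will be 9 months.

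Statistical methods {20a} specifies a covariance pattern mixed model that uses all post-randomisation time points. It takes an estimate at each, with the first follow-up as primary. Section {20c} adds that this model can include participants who respond at some time points and not others.

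**The concern.** An infection that comes after an assessment cannot have changed the score recorded there. The exclusion window runs to the end of follow-up while the primary endpoint sits at its first visit. For that endpoint, the rule therefore removes people whose score COVID-19 could not have touched.

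Two things follow. The sensitivity analysis loses precision without gaining protection at the primary time point. It also conditions on an event after randomisation over a longer window than the question needs, which gives more room for the remaining groups to differ from those randomised. If the result departs from the primary analysis, a reader cannot tell whether COVID-19, selection or lost precision is the cause.

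**Working it through.** **Logic of the rule.** Take three participants, all with a PCS score at the first follow-up.

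1. Reports COVID-19 at the first follow-up. The article's rule removes this person. A rule working by assessment sets the first and all later scores to missing, so the person also drops out of the model.
2. First reports COVID-19 at the second or third follow-up. The article's rule removes everything. A rule by assessment keeps the first score.
3. Never reports COVID-19. Kept under both rules.

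The rules differ only for the second kind of participant, and there the discarded first score preceded the infection.

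**Reproducing the sample size.** Sample size {14} gives a difference of 4, an SD of 8, 80% power, 5% two-sided alpha, 45% non-collection and 15% lacking capacity.

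- Per arm: 2 × (1.96 + 0.8416)² × (8/4)² = 62.8, so 63, or 126 in total. The t-test version gives 64 per arm, 128 in total.
- Inflated in sequence: 126/(0.55 × 0.85) = 269.5 and 128/(0.55 × 0.85) = 273.8. The stated 272 lies between them.
- Analysable at the first follow-up: 272 × 0.55 × 0.85 = 127.2, with power 0.80.

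**Illustrative size.** The documents give neither COVID-19 incidence nor time to the first follow-up. Assumptions: a proportion R of 10% to 30% infected over follow-up of length T, a constant hazard, and the first follow-up at t = 2 to 6 months.

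- Infected before the first follow-up: B = 1 − (1 − R)^(t/T).
- Share of those excluded who were infected after it: (R − B)/R.
- Power with m participants: Φ(0.5 × √(m/4) − 1.96), where m = 127.2 × (1 − R) under the article's rule and 127.2 × (1 − B) if only earlier infections count.

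Worked case, R = 20%, T = 12, t = 4: B = 1 − 0.8^(1/3) = 0.072, and the share is (0.20 − 0.072)/0.20 = 0.64. The article's rule leaves 101.7 participants (power 0.713). Excluding earlier infections only leaves 118.0 (power 0.775).

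For T = 12 months, with each range running from t = 2 to t = 6:

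| R | Left, any-time rule | Power, any-time rule | Power, earlier infections only | Share infected after first follow-up |
|---|---|---|---|---|
| 10% | 114.4 | 0.763 | 0.798 to 0.784 | 0.83 to 0.49 |
| 20% | 101.7 | 0.713 | 0.790 to 0.760 | 0.82 to 0.47 |
| 30% | 89.0 | 0.655 | 0.781 to 0.732 | 0.81 to 0.46 |

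With T = 9 months, the share runs from 0.77 down to 0.29, and power with earlier infections only from 0.796 down to 0.706.

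**The case against.** **Purpose.** The article speaks of outcomes in the plural, the model estimates effects at every time point, and falls are counted over the whole follow-up. Infection after the first visit matters for those later results. This is correct, and it means that the late exclusions are needless for the first follow-up contrast only. It does not rescue removal of the whole person, because exclusion by assessment covers the later time points as well and keeps the earlier scores.

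**Selection.** Any exclusion for COVID-19 conditions on a post-randomisation event, including the alternative proposed here. This stands; the difference is one of degree. A reader might go further and infer that infection differs by arm, for instance through installers or carers in the home. The documents contain nothing on infection by arm, so bias in a particular direction is not shown.

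**Size.** A sensitivity analysis is read for consistency of the estimate more than for power. The figures above also rest on assumed incidence and timing, the full 45% non-collection, and an unadjusted comparison where the planned model adjusts for baseline PCS. The Discussion reports longer waits in both groups, so the first follow-up may come late, which would shrink the share infected afterwards. All of this stands.

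**Data collection.** A reader might infer that the analysis depends on COVID-19 status recorded only at baseline. Section {18a} lists "participant demographics, property tenure, COVID-19 status and several outcome measures" at baseline, whereas "at the three subsequent data collection time points, participants who are able to answer questions themselves will complete a questionnaire comprised of the SF-36" opens a follow-up list without COVID-19 status. The documents do not support that inference. The exclusion is worded by what participants indicated about the follow-up period, which presupposes a report during follow-up. The lists are also incomplete: for self-reporting participants they omit perceived difficulty in bathing, which Secondary outcomes says is collected at every time point. The schedule figure and the full protocol are not shown.

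**Conclusion.** The point holds for the timing of the exclusion. As worded, the rule discards first follow-up scores that preceded infection, and it selects on a post-randomisation event more broadly than its purpose requires.

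The existence of the fault follows from the text alone; its size does not. Under a constant hazard, 12-month follow-up, 10% to 30% infected and a first follow-up at 2 to 6 months, about 46% to 83% of exclusions would be of people infected after the primary outcome was measured. Power at that visit would be about 0.76 to 0.66, against about 0.80 to 0.73 if only earlier infections were excluded.

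The intention-to-treat primary analysis and the target of 272 are untouched. This is a small improvement to one sensitivity analysis. It is not evidence that the COVID-19 data are missing or that the trial's conclusion is at risk.

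**What to change.** In this sensitivity analysis, set to missing only the assessments at or after the first follow-up at which the participant reports COVID-19, and keep all earlier assessments in the planned repeated measures model. Report the number with COVID-19 by arm and time point beside the result, so that readers can judge the scope for selection.

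No infection date is needed: the follow-up at which COVID-19 was first reported is enough. The cost is a sentence in the analysis text and a small change to the code.

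The downside should be stated with the result. The analysis still conditions on a post-randomisation event, though less than the current rule does, and the model treats the removed scores as missing at random given the scores that are kept.
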